## The program abstract

|                                                                                                  |                                                                                                                                                                                                                                                                                                                                                                                                                                                                                       |
|--------------------------------------------------------------------------------------------------|---------------------------------------------------------------------------------------------------------------------------------------------------------------------------------------------------------------------------------------------------------------------------------------------------------------------------------------------------------------------------------------------------------------------------------------------------------------------------------------|
| Research topic                                                                            | Multi-center, Randomized, Double-blind, Controlled Study of the Effectiveness and Safety of Mifepristone in Treating Adenomyosis                                                                                                                                                                                                                                                                                                                                               |
| Trial objective                                                                           | To investigate the effectiveness and safety of mifepristone in treating adenomyosis                                                                                                                                                                                                                                                                                                                                                                                                   |
| Trial drug
Active ingredient
Dosage
Approach
Time | Mifepristone tablets
Mifepristone
10 mg daily
Orally
Twelve weeks                                                                                                                                                                                                                                                                                                                                                                                                         |
| Trial drug
Active ingredient
Dosage
Approach
Time | Placebo
N/A
N/A
One tablet daily, orally
The longest 12 weeks                                                                                                                                                                                                                                                                                                                                                                                                             |
| Indication                                                                                | Adenomyosis meeting the criteria                                                                                                                                                                                                                                                                                                                                                                                                                                                      |
| Research design                                                                           | Multi-center, randomized, double-blind, allocation concealment, placebo-controlled, parallel grouping                                                                                                                                                                                                                                                                                                                                                                                 |
| The type of control                                                                       | 12 weeks of placebo control                                                                                                                                                                                                                                                                                                                                                                                                                                                           |
| Inclusion criteria                                                                        | 
 
1. Women had a diagnosis of adenomyosis by B-ultrasound or pelvic MRI examination and the volume of their uterus were less than those with 10 weeks of pregnancy
 
2. Women with 10-cm visual analogue scale (VAS) of adenomyosis-associated pain > 0 point with or without menorrhagia (PBAC<math>\geq</math>100 points)
 
3. Women between 18 and 50 years of age who currently have no childbearing requirement
 
 |

Multi-center, Randomized, Double-blind, Controlled Study of the Effectiveness and Safety of Mifepristone in Treating Adenomyosis

|                           |                                                                                                                                                                                                                                                                                                                                                                                                                                                                                                                                                                                                                                                                                                                                                                                                                                                                                                                                                                                                                                                                                                                                                                                                                                                                                             |
|---------------------------|---------------------------------------------------------------------------------------------------------------------------------------------------------------------------------------------------------------------------------------------------------------------------------------------------------------------------------------------------------------------------------------------------------------------------------------------------------------------------------------------------------------------------------------------------------------------------------------------------------------------------------------------------------------------------------------------------------------------------------------------------------------------------------------------------------------------------------------------------------------------------------------------------------------------------------------------------------------------------------------------------------------------------------------------------------------------------------------------------------------------------------------------------------------------------------------------------------------------------------------------------------------------------------------------|
|                           | 
 
4. Women who had normal cervical cytology test
 
5. Women who agreed to choose a barrier method of contraception
 
6. Women who agreed to adhere to the study requirements and signed the informed consent
 
7. Women who were not postmenopausal
 
                                                                                                                                                                                                                                                                                                                                                                                                                                                                                                                                                                                                                                                                                                                                                                                                                                                                                                                                                                    |
| Exclusion criteria | 
 
1. Patients with HB < 90G/L
 
2. Patients with undiagnosed abnormal vaginal bleeding or endometrial lesions
 
3. Patients who were preparing to give birth when taking the medication or within 6 months of stopping the medication
 
4. Patients with malignant tumors (including the reproductive system and other systems);
 
5. Patients with severe heart, liver, kidney disease and adrenocortical insufficiency
 
6. Patients who had the results of follow-up laboratory test indicating abnormal clinical significance
 
7. Patients who had a known allergy to mifepristone, or related compounds
 
8. Patients with any other diseases or conditions that may cause the study drug to alter absorption, accumulate excessively, affect metabolism, or change the excretion pattern
 
9. Patients with clinically significant depression within the current or most recent year
 
10. Patients who regularly took analgesics due to other underlying diseases
 
11. Patients used the drugs, such as Ketoconazole, itraconazole, erythromycin, rifampicin, corticosteroids (hydrocortisone, prednisone, dexamethasone, etc.), and some anticonvulsants
 
 |

Multi-center, Randomized, Double-blind, Controlled Study of the Effectiveness and Safety of Mifepristone in Treating Adenomyosis

|                                |                                                                                                                                                                                                                                                                                                                                                                                                                                                                                                                                                                                                                                                                                                                                                |
|--------------------------------|------------------------------------------------------------------------------------------------------------------------------------------------------------------------------------------------------------------------------------------------------------------------------------------------------------------------------------------------------------------------------------------------------------------------------------------------------------------------------------------------------------------------------------------------------------------------------------------------------------------------------------------------------------------------------------------------------------------------------------------------|
|                                | 
(phenytoin, phenobarbital, carbamazepine, etc.), griseofulvin, non-steroidal anti-inflammatory drugs (aspirin, acetaminophen, etc.) and couldn't be stopped during the study
 
12. Patients currently used any other hormone drugs, including: a. use of GnRH agonists within 6 months before the screening period; b. use of progestins or danazol and other long-acting hormones within 3 months before the screening period; c. use of oral contraceptive-like short-acting hormones within one month before the screening period;
 
13. Patients who participated in other clinical trials within 3 months before the screening, or who were considered inappropriate to participate in the study by other investigators.
 |
| Number of subjects      | Subjects are screened and 150 subjects are randomized into groups.                                                                                                                                                                                                                                                                                                                                                                                                                                                                                                                                                                                                                                                                             |
| Safety indicator        | 
(1) General observation items: gynecological examination, blood pressure, heart rate, weight
 
(2) Auxiliary examination: pelvic ultrasonography (uterine volume, endometrium), magnetic resonance (non-essential), breast B ultrasound, sex hormones, blood routine, coagulation function, liver and kidney function, blood lipid, blood/urine pregnancy test, and endometrial biopsy (if necessary)
 
(3) Adverse Event Monitoring: adverse events, drug side effects and adverse drug reactions
                                                                                                                                                                                                                            |
| Effectiveness indicator | 
(1) Changes in chronic pelvic pain associated with adenomyosis (VAS scale)
 
(2) Changes in uterine bleeding (PBAC scale)
 
(3) Improvement of anemia (blood routine)
 
(4) Size of the uterus
                                                                                                                                                                                                                                                                                                                                                                                                                                                                                                                           |

Multi-center, Randomized, Double-blind, Controlled Study of the Effectiveness and Safety of  
Mifepristone in Treating Adenomyosis

## Abbreviations

| Abbreviation | Name                                  |
|--------------|---------------------------------------|
| ALT          | Alanine aminotransferase              |
| APTT         | Activated partial thromboplastin time |
| AST          | Aspartate aminotransferase            |
| BUN          | Blood urea nitrogen                   |
| Cr           | Creatinine                            |
| E2           | Estradiol                             |
| FSH          | Follicular estrogen hormone           |
| HB           | Hemoglobin                            |
| HCG          | Human chorionic gonadotropin          |
| HDL          | High-density lipoprotein              |
| LH           | Luteinizing hormone                   |
| N/A          | Not Applicable                        |
| PBAC         | Pictorial blood loss assessment chart |
| PLT          | Platelet count                        |
| PT           | Prothrombin time                      |
| RBC          | Red blood cell count                  |
| TBIL         | Total bilirubin                       |
| TC           | Total cholesterol                     |
| TG           | Triglyceride                          |
| VAS          | Visual analogue scale                 |

Multi-center, Randomized, Double-blind, Controlled Study of the Effectiveness and Safety of  
Mifepristone in Treating Adenomyosis

## 1. Introduction

### 1.1 Research Background

Uterine adenomyosis is a common benign disease in gynecology. Most of them have secondary, progressive dysmenorrhea and menorrhagia as the main clinical manifestations, which seriously endanger the patient's physical and mental health. Most patients have the desire to retain the uterus, so the conservative treatment of drugs is dominant in the treatment of adenomyosis. However, the current various clinical medications of adenomyosis still have limitations and need to be improved, so it is imperative to expand the clinical drug use of adenomyosis [1]. Mifepristone is defined as a selective progesterone receptor modulator. Under certain conditions, it acts as an antiprogesterin, inhibits endometrial proliferation, inhibits ovulation, and can cause reversible amenorrhea. Therefore, in recent years it has been widely used in uterine fibroids, endometriosis and other hormone-dependent gynecological diseases [2-5]. Adenomyosis is also associated with hormone-related diseases, especially with endometriosis closely. The protocols of clinical drug treatment are similar between them. At present, domestic research on mifepristone for the treatment of adenomyosis is relatively extensive. A large number of domestic reports have reported that short-term treatment of adenomyosis with low-dose mifepristone is safe and effective [6, 7]. During the treatment with mifepristone, most patients had amenorrhea, which significantly reduced dysmenorrhea and decreased menstrual flow. The effect on reducing the size of the uterus and lesions of patients with adenomyosis was significant [8, 9]. However, the majority of domestic literatures were small sample case-control studies or retrospective studies. There is no randomized, double-blind, controlled study. The clinical study of adenomyosis treated with Mifepristone is not found overseas. Therefore, the clinical evidence is insufficient, and high-quality randomized controlled trials are still needed.

This project intends to use multi-center, randomized, double-blind, controlled clinical trials to explore the effectiveness and safety of mifepristone (10 mg) for the treatment of symptomatic adenomyosis, which is a new clinical study of the old drug.

### 1.2 Research principle

Mifepristone is a selective progesterone receptor modulator. Foreign high-quality literatures have proved that it is effective for low-dose and short-term treatment of uterine fibroids and endometriosis. The purpose of this study was to confirm the effectiveness and safety of mifepristone (10 mg) for the treatment of symptomatic adenomyosis.

### 1.3 Benefit - Risk Analysis

## Multi-center, Randomized, Double-blind, Controlled Study of the Effectiveness and Safety of Mifepristone in Treating Adenomyosis

In recent years, the clinical studies at home and abroad have proven that oral mifepristone treatment can reduce the volume of adenomyosis, achieve amenorrhea, relieve dysmenorrhea, improve anemia due to more bleeding, relieve clinical symptoms, and the treatment costs are relatively cheap. No significant adverse reactions were found in previous studies. Early studies showed that in early/middle follicular levels, GnRH-a low estrogen status was less likely to occur. The psychological, life, economic, and other damages and adverse effects of the subjects were rarely caused. Only a few individuals experienced some known minor adverse side-effects after taking the drug. We define adverse events in detail in the study, and regularly check the various biochemical indicators of the patients and monitor endometrial thickness through pelvic ultrasound, etc. If the ultrasound results show endometrial thickness  $\geq 12\text{mm}$ , endometrial biopsy is recommended to be performed. If the patient develops any discomfort during the study, or if there is a new change in the condition or any unexpected condition, regardless of whether it is related to the drug, the researchers will make judgments and medical treatment.

## 2. Research purposes

The main purpose of this study was that the visual analogue scale (VAS) was used as the main evaluation index to investigate whether daily oral mifepristone of 10 mg was superior to placebo in the treatment of symptoms of adenomyosis-associated pelvic pain.

The secondary purpose is to evaluate the pictorial blood loss assessment chart (PBAC), uterine volume, hemoglobin changes, and the safety of this dose (eg, adverse events, vagina bleeding, gynecological safety).

## 3. Researchers and other research participants

In this study, the main project leader is [name] from Women's Hospital, School of Medicine Zhejiang University. The principal researchers must sign their names in the signature page of this program before each research center begins to recruit subjects. Similarly, before all program revision plans/integration plans become effective in the corresponding center, both name and date must be signed by the principal researchers. A complete list of all participating centers and their researchers, as well as all required signature files, will be kept in the research documents of the sponsor.

## 4. Research design

### 4.1 Overview of research design

This multicenter study is performed in 150 subjects who are diagnosed as adenomyosis by B-ultrasonography or magnetic resonance imaging (MRI) and had related symptoms (dysmenorrhea, with or without large doses).

Twelve weeks of randomization, allocation concealment, double-blind, placebo-controlled, parallel grouping. Subjects are randomly assigned to one of two treatment groups and received one of the following treatments: (1) Mifepristone tablets of 10mg, 1 tablet daily, oral; (2) Placebo, 1 tablet daily, oral.

### 4.2 The sketch map of research design

[figure not shown]

### 4.3 Rationality of research design

In order to avoid selection bias or bias by any other investigators' or subjects' understanding of the treatment used, the trial design was performed according to the principles of randomization, allocation concealment, double-blind, placebo control. The placebo control is necessary because of the more pronounced placebo effect observed in literature studies.

Multi-center, Randomized, Double-blind, Controlled Study of the Effectiveness and Safety of Mifepristone in Treating Adenomyosis

From an ethical point of view, placebo-controlled trials are considered acceptable because they allow the patients in the study to receive analgesics other than research drugs (indomethacin suppositories), which have been passed by the ethics Committee of Women's Hospital, School of Medicine Zhejiang University.

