5.3.1 Quit decided by the researchers

Refer to the fact that the subject who has already been selected cannot continue to conduct the test during the trial. The researcher decided that the case quit the trial.

(1) In the course of the study, if the subject's condition is aggravated (which is defined as: after at least 4 weeks of treatment, the formerly symptomatic subject has aggravated symptoms that severely affect life; or the patient with no previous symptoms has or develops new adenomyosis related symptoms that severely affect life; or abnormalities such as adenomyosis/ intima, and so on, found by the B-ultrasonic examination during the study period, and other researchers believe that the condition is aggravated), in order to protect the subject, let the subject complete the safety check and withdraw from the test and receive other effective treatments;

(2) In clinical trials, subjects have some comorbidities, complications, or special physiological changes that were not suitable for continued trials;

(3) Use of other treatments or drugs which are prohibited to be combined with each other, affects the judgment of effectiveness and safety.

(4) The subject has adverse events and serious adverse events (such as acute allergic reactions), who is not suitable to continue to undergo the trial;

(5) The use of the drug is less than 80% of the prescribed amount or more than 120% of the prescribed amount, but the clinical recovery standard is reached after the medication is not fully used, and the subject applies for the termination of the drug. With the consent of his/her responsible doctor, the remaining drugs can be returned and a separate description of compliance issues can be made;

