## 6.8 Combining medication and treatment

(1) In addition to the trial drug, it is forbidden to use other Chinese and Western drugs treating this disease that are the same or similar to the functional indications of mifepristone tablets in the observation period, and other drugs and treatment methods that affect the evaluation of the efficacy of this trial, including other contraceptive drugs (such as progestin contraceptives, estrogen-progestin contraceptives, etc.); and drugs that interact with mifepristone (such as ketoconazole, itraconazole, erythromycin, etc., and rifampicin, corticosteroids, and some anticonvulsants, griseofulvin, non-steroidal anti-inflammatory drugs, and so on). Please refer to the instructions for drug interactions for details. It is forbidden to take painkillers and hemoglobin drugs privately without the consent of a doctor.

(2) During the study period, the endometrium thickness of the B-ultrasonic examination should be recorded in the eCRF. If the researcher suspects endometrial hyperplasia, hysteroscopy or curettage examinations can be performed if necessary, and with reference to clinical routine treatment, the study medication can be discontinued or continue to be used.

(3) During the observation period, the name, usage and dosage, and time of taking of drugs or other treatments that must be taken for other comorbid diseases, must be recorded in the electronic case report form.

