## 15.4 Selection of statistical analysis data

Full Analysis Set (FAS): According to the basic principles of intentionality analysis (ITT), statistical analysis is performed on all randomized cases and patients without any valid data at baselined will be excluded. For the uncompleted clinical trial observations data, last-observation-carry-forward is conducted at the end of the trial. The number of subjects whose efficacy will be evaluated at endpoint is the same as at the beginning of the trial. Per Protocol Set (PPS): All data from those well compliant subjects (taking 80% to 120% of the applied trial drug dose), which compliant with the protocol and have not taking the prohibited drug during the trial, as well as have VAS assessed at baseline, and have at least one follow-up VAS record. Safety Set (SS): All subjects who were randomized and have taken at least once clinical trial drug and have at least once safety evaluation should be evaluated for safety.

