### (2) Case characteristics

Enrollment and completion: Summarize the number of cases enrolled and completed by each center, and list the unfinished cases and cases that do not enter each population.

Multi-center, Randomized, Double-blind, Controlled Study of the Effectiveness and Safety of  
Mifepristone in Treating Adenomyosis

(3) General information and baseline characteristics

The baseline is defined as Interview 1 (Day 0-3), and the SS is evaluated at baseline.

Baseline descriptions are made on the age, sex, allergy history, medication history, history of illness, and laboratory tests for each group of population.

(4) Analysis of safety indicators

The SS population is used for analysis.

Describe the number of occurrences of adverse events and adverse reactions of the total and each group and give the corresponding list in the detailed account.

Compared with the laboratory tests before the treatment, the situations after the treatment of each interview are described in the form of the crosstabs, and the abnormalities that are significant after the treatment are listed.

The vital signs indicators of each interview relative to the baseline during interviews and after treatment are described, and t-test or non-parametric test is used for intragroup comparison.

(5) Analysis of efficacy indicators

FAS and PP populations are used for analysis.

Baseline: Baseline description of each efficacy indicator.

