**Primary effectiveness variable**

The primary effectiveness variable is assessment of adenomyosis-associated pain by VAS at week 12 (at the end of the double-blind portion) and compared with baseline period (interview 2). Using the covariance analysis (ANCOVA), baseline VAS scores are used as covariates to compare the differences in the VAS scores at the 12th week. At the same time, comparisons were made during each interview (interview 2-5). For the missing data, the method of Last Observation Carried Forward (LOCF) will be used. Further details of the method can be found in the statistical analysis plan.

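### The indomethacin rescue that makes placebo ethically acceptable in section 4.3 falls under the NSAID ban in section 6.8(1), which has no exemption for it

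*Protocol*

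**What the plan says.** Section 4.3 (Rationality of research design) defends the placebo arm on the ground that "they allow the patients in the study to receive analgesics other than research drugs (indomethacin suppositories"), and adds that the ethics committee of the lead hospital has passed this. No other rescue drug is named anywhere in the protocol.

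Section 6.8(1) lists what is forbidden during the observation period. Three parts of it matter here:

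- It bans "drugs that interact with mifepristone (such as ketoconazole, itraconazole, erythromycin, etc., and rifampicin, corticosteroids, and some anticonvulsants, griseofulvin, non-steroidal anti-inflammatory drugs", and the list then runs on.
- It bans "other drugs and treatment methods that affect the evaluation of the efficacy of this trial".
- It ends: "It is forbidden to take painkillers and hemoglobin drugs privately without the consent of a doctor".

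Three later rules depend on what counts as prohibited:

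- Section 5.3.1(3) gives this ground for withdrawal by the researcher: "Use of other treatments or drugs which are prohibited to be combined with each other, affects the judgment of effectiveness and safety".
- Section 15.4 limits the per-protocol set (PPS) to well-compliant subjects "which compliant with the protocol and have not taking the prohibited drug during the trial".
- Section 15.5(5) says of the efficacy analyses that "FAS and PP populations are used for analysis", and the primary-variable paragraph adds: "For the missing data, the method of Last Observation Carried Forward (LOCF) will be used".

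**The concern.** The two sections give a site opposite instructions about the same drug. A doctor working from 4.3 would offer the suppository. A doctor working from 6.8(1), the section that governs concomitant medication, would withhold it, or would treat its use as a violation.

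Two things are at stake. The first is patient care: the ethical case for placebo rests on an analgesic that the operative rule forbids. The second is the primary result. The endpoint is a pain VAS at week 12, so whether a woman receives an analgesic, stays in the trial and enters the PPS all bear on what is measured and on whom. Every participant enters with pain (VAS above 0, section 5.1), so requests for rescue are foreseeable.

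**Working it through.** There is no figure to recompute. The check sets the provisions side by side.

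1. **Is the rescue drug in the banned class?** Section 4.3 names indomethacin. Section 6.8(1) names NSAIDs by class among the drugs that interact with mifepristone. Indomethacin is an NSAID, so it is caught.

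2. **Is there a second ground?** Section 6.8(1) also bans treatments that affect the efficacy evaluation. The primary variable is pain, so an analgesic fits those words. This ground is weaker, because the examples that follow it are contraceptives. The conflict does not depend on it.

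3. **Is there an exemption?** None is stated in 6.8(1), 5.3.1 or 15.4. The nearest candidate is the doctor's-consent sentence. It is a further prohibition, aimed at private use. It suggests that some painkillers may be taken with consent, but it names none, does not refer to 4.3 and does not qualify a ban imposed because of interaction. A doctor could consent to a painkiller outside the NSAID class and satisfy both rules, and could not do so with indomethacin. Acetaminophen is not clearly open either, since exclusion (11) in section 5.2 lists it as an example of an NSAID.

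4. **Does exclusion (11) add to the conflict?** Not directly. It concerns women already using listed drugs that could not be stopped during the study, not rescue started during treatment.

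5. **What follows if 6.8(1) is applied as written?**
   - Withdrawal under 5.3.1(3) becomes available. It is the researcher's decision and is not automatic.
   - If she is withdrawn before week 12, an earlier VAS is carried forward in the full analysis set (15.4 and 15.5).
   - She does not meet the PPS definition, whether or not she is withdrawn.
   - Monitoring under 15.1 checks for use of prohibited drugs, so a monitor could flag the suppository on which 4.3 relies.

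6. **Could this differ between arms?** The sample-size section expects more pain at week 12 on placebo (mean 3.25) than on mifepristone (2.01). Rescue use, and any loss that follows from it, could plausibly be more frequent on placebo. This is an inference; the protocol gives no rescue data.

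7. **Is there any related number?** The sample-size section adds 25% to 60 per group: 60 × 1.25 = 75, so 75 − 60 = 15 per group, and 15/75 = 20% of those randomised. That allowance covers loss to follow-up, protocol violations, compliance and other factors together. Rescue users who were withdrawn or classed as violators would come out of it. It says nothing about how many there would be and is not a measure of the effect.

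**The case against.** The best counter-argument is that the protocol can be read consistently. Section 4.3 names one drug in one form with ethics approval, 6.8(1) is a general list, and the consent sentence would have little work to do if every pain-relieving drug were banned outright. On that reading the rule is no self-medication, the suppository is available through the doctor, and the defect is a missing cross-reference. This is probably what the authors meant. It is not what 6.8(1) says: the class ban rests on interaction, and consent to painkillers in general does not remove it. A site should not have to infer the exemption.

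Four further points can be made:

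- **The interaction list refers to the product instructions.** Those are not at hand, so the scope of the NSAID caution for short rectal use cannot be settled here. That stands, but it is a reason for the protocol to state its position.
- **The consequences are conditional.** This also stands. Withdrawal is discretionary, carry-forward applies only if the week-12 VAS is missing, and no site is shown to have refused rescue.
- **PPS membership is often settled in the statistical analysis plan.** That plan is not shown and may define deviations. It cannot, however, tell an investigator whether to give the suppository.
- **There is no magnitude.** That is correct, and none is claimed.

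**Conclusion.** The contradiction holds. The only rescue analgesic named in the protocol, and the stated basis for accepting placebo, belongs to a class that the concomitant-medication rule forbids without exception. This is a stated rule that gives the wrong result when followed, not detail left to another document, and it should be fixed.

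The finding rests on the text and on indomethacin being an NSAID. The effect on the treatment estimate, power or PPS size is unknown: the protocol gives neither a rescue rate nor an effect of rescue on VAS. The downstream effects on withdrawal, carried-forward scores and PPS membership are possible and depend on how sites apply the rule.

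**What to change.** Add one sentence to 6.8(1), to this effect: *Indomethacin suppositories given with the doctor's consent for adenomyosis pain are permitted rescue, and their use does not count as prohibited-drug use for section 5.3.1(3) or for the PPS in section 15.4.*

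Enter the date and dose of each use in the concomitant-drug record already scheduled at weeks 4, 8, 12 and 16, and keep collecting VAS from women who use it. Because 6.8(1) lists NSAIDs as interacting drugs, the sponsor should confirm against the product instructions that this use is acceptable, and state any dose limit it considers necessary. Exclusion (11) needs no change.

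The cost is one sentence and entries in an existing record. As a protocol change it needs ethics committee approval under section 17. Design, visit schedule and sample size are unaffected.
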